**A. Background and Significance/Relevance**

Childhood obesity has rapidly increased to reach epidemic proportions. As of 2012, nearly one third of children in the United States can be classified as overweight or obese, raising concern for a number of both short and long-term health consequences (CDC, 2015; Ogden et al., 2014). Increased childhood weight has been linked to leisure time sedentary activity (Strasburger, Jordan & Donnerstein, 2012). Therefore, reducing children’s sedentary activity and encouraging physical activity and have become major public health goals.

The majority of sedentary time takes the form of screen-based activities, including video games, television, computer games, phones, and tablets. In an effort to merge children’s favorite activities; sports and video games, and to help the player be more physically active (ACSM, 2016; Altamimi & Skinner, 2012), game developers have incorporated physical movements into game play. “Active video games” (AVGs) are now being studied as a method to increase children’s interest and participation in physical activity. Although research indicates that AVG playing may lead to energy expenditure comparable to light to moderate physical activity (Peng, Ling, & Crouse, 2011; Roemmich et al., 2012), children prefer sedentary video games to AVGS and often find such active games to be boring (Simons et al., 2015a; Simons et al., 2012). Children do not play AVGs as often or with the same intensity as traditional games/sports (Roemmich et al., 2012) and lose interest in them (Simons et al., 2015a); efforts must be made to increase the appeal of AVGs so they are competitive with sedentary video games.

Self-determination theory has been applied to the study of physical activity adoption and adherence (Teixeira et al., 2012). Self-determination theory posits that intrinsic motivation, or desire to engage in an activity because of enjoyment or personal fulfillment, might be increased through autonomy (Ryan & Deci, 2002). Past research has shown that increased autonomy via choice of how and when an activity is engaged in may help increase intrinsic motivation and therefore make an activity more appealing (Roemmich et al., 2012). Such increased internal motivation may help increase the relative reinforcing value (RRV) of AVGs, increasing the attractiveness of AVG games and making them a more competitive option compared to the already reinforcing sedentary games and thereby leading children to play active video games more often and more intensely than sedentary video games.

Ideally, increasing the RRV of AVG, would lead to increased motivation to play both the AVG and traditional forms of the activities upon which AVGs are based. Both AVG play and traditional games would lead to increased physical activity and greater energy expenditure. The magnitude of increase in energy expenditure would be greatest if AVG play served as gateway for traditional game play, as traditional forms of active games produce greater energy expenditure (Roemmich et al., 2012). However, AVGs’ may not serve as a gateway to increasing the motivation to engage in traditional games. Current research suggests that providing children with AVGs does not make them more active in general (Baranowski et al., 2012). There is no correlation between hours spent playing active video games and physical activity, but, rather, children who regularly play AVGs show a preference for other screen-based entertainment, such as television and sedentary video games (Simons et al., 2015b). Indeed, children often prefer sedentary video games to AVGs (Simons et al., 2012). It is therefore of concern that increasing children’s exposure to AVG may inadvertently increase their motivation to play sedentary video games rather than traditional sports/games thereby increasing sedentary time and decreasing overall energy expenditure. This tendency towards increased sedentary behavior may be further compounded by increased energy intake, especially in the form of energy-dense snacks and drinks (Pearson & Biddle, 2011). This study will examine whether the RRV of AVG may be increased by providing greater autonomy and whether increasing the RRV of AVG also increases the RRV of sedentary video games.

**B. Overall Objective and Specific Hypotheses to be tested**

The goal is to investigate how autonomy might be used to increase children’s intrinsic motivation towards active video games, active play, and/or sedentary activity. Specific hypotheses include:

**H1a (Primary):** High autonomy of AVG play will result in increased reinforcing value of AVGs relative to sedentary video games. Lower autonomy of AVG play will not show an increased reinforcing value of AVG relative to sedentary video games.

**H1b**: High autonomy of AVG play will increase intrinsic motivation to play AVGs relative to low-autonomy control condition.

**H1c:** High autonomy of AVG play will increase intrinsic motivation to engage in physical activity relative to low-autonomy control condition.

**H1d:** High autonomy of AVG play will result in more hours of AVG play during the follow-up phase relative to the low-autonomy control condition.

**H1e:** High autonomy of AVG play will increase usual physical activity during the follow-up phase relative to the low-autonomy control condition.

**H1f:** High autonomy of AVG play will result in increased reinforcing value of AVGs relative to traditional active games.

**H2a:** Increased reinforcing value of AVGs will result in increased reinforcing value of sedentary video games.

**H2b:** Increased reinforcing value of AVGs will result in increased hours/week spent playing sedentary video games.

**H2c**: Increased reinforcing value of AVGs will result in increased time spent in other screen-based sedentary activities (television, computer games, tablets/cell phones).

**H2d:** Increased time spent in screen-based sedentary activities will result in increased sweetened beverage/snack consumption.

**C. Methods**

**i. Participants and Screening:**

Participants for this study will consist of healthy sedentary children (ages 8-12 y). Sedentary behavior shall be operationalized, similar to previous studies (Epstein et al., 2011; Tremblay et al., 2011), as engaging in at least 14 hours of screen-based leisure time sedentary behavior (sedentary video games, television, computer games, cell phone/tablet) per week. Both non-overweight and overweight children (5^th^-95th BMI percentile) will be included. Initial screening will take place using a Survey Monkey based questionnaire. Entry criteria will include not currently trying to lose weight, no medical conditions which might impede physical activity, not engaging in leisure time moderate to vigorous physical activity more than three times per week for one hour at a time, not currently or previously owning an active video game system, not playing an active video game more than one-half hour per week, willingness to adhere to study treatments and measurement schedules, and access to a cellular phone to complete activity recall questionnaires Parents will provide informed consent and children will provide written assent before participation. The study will be approved by the University of North Dakota Institutional Review Board.

**ii. Design:**

The overall design will be a 2 group factorial design with autonomy condition treated as a between subject variable (high autonomy, low autonomy). Participants will be randomly assigned to a high autonomy group or a low-autonomy group. Time (baseline, end of 6 week intervention, 4 week follow-up) will be treated as a within-subject variable. Participants will be blocked according to Taves minimization on gender (male vs female), BMI (above 85^th^ percentile vs. below 85^th^ percentile), and baseline liking of AVG (7 and lower vs. 8-10 on 10 point Likert scale).

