*Baseline RRV Assessments:* RRV assessments will take place in the Grand Forks Human Nutrition Research Center (GFHNRC) laboratory space at Choice Health and Fitness Center. On separate days children will be assessed for their relative reinforcing value of active to sedentary video games (RRV_video games_) and RRV of active video games to traditional active games (RRV_active games_). Order of these tests will be counterbalanced among participants. Participants will be asked to sample and rate their liking of four active video games (Appendix 12), four inactive video games (Appendix 13), and four traditional games/sports (Appendix 14). Children will be permitted to briefly sample games with which they are not familiar. Following the RRV task, children will be permitted to play the games corresponding to time earned on the task. Active and sedentary video games shall be played at Choice Health and Fitness spaces. Participants and their parent will complete a 24 hour recall assessing baseline time spent in physical activity, sedentary video games, and other screen-based sedentary activities at the end of one of these visits. Parents and children will complete the 3^rd^ and 4^th^ of the 4 recalls during weekend days at home using SurveyMonkey.

*Week 1 and 3 Assessments:* Children will wear an activity monitor for 7 consecutive days in the same manner as at baseline assessment. Participating parents and children will also be asked to fill-out the 24 hour activity recall on 4 days, including at least one weekend day.

*End of-intervention (Week 6) Assessments:* Outcome assessments will take place during and just after the last week of the 6 week intervention. Post-intervention anthropometry, questionnaire, RRV, and physical activity testing will be identical to screening/baseline assessments.

*4 Week (Week 10) Post-Intervention Follow-up Assessments and Debriefing:* At 4 weeks following the end of the intervention, participants will complete their final assessment, to determine whether intervention effects on videogame reinforcement, AVG use, physical activity reinforcement, physical activity, and sedentary behavior have been maintained for at least 4 weeks. The assessments will be identical to screening/baseline. Following the assessment, participants will be debriefed, asked for intervention feedback (Appendix 15 & 16), thanked for their time, and compensated.

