**iv: Intervention:**

Participants will be randomly assigned to a high or low-autonomy group. Children in each group will be given an active video game system to use while enrolled in the study, and active video game DVDs requiring full body movements to operate. To evaluate whether AVG play impacts their motivation to engage in sedentary screen-based activities, children will also be given sedentary video games which can be operated using only hand and finger movement. To better simulate naturalistic conditions, the intervention will take place in participants’ homes. After both baseline RRV_activite games_ and RRV_video games_ have been assessed the intervention will commence. A researcher will visit the home at baseline to explain the intervention, set-up the AVG system, train the child and a parent on use of the system, and provide the activity monitor that the child will wear throughout the first, third, and sixth week of the intervention to track physical activity and sedentary behavior. The researcher will also provide a log and ask the child to record the date, duration of play, which game was played, and with whom as a check of study fidelity (Appendix 17). The researcher will stress to the child and parent the importance of following the research protocol, including wearing the activity monitor and recording AVG/video game play.

Children in the high autonomy group will be given two AVG games of their choice. Children in the low autonomy group will be given their most-liked game from the previous baseline RRV assessment. After two weeks, a researcher will return to the home to monitor progress and exchange the AVG and sedentary games. At each exchange, children in the high autonomy group will be allowed to select their next game, while children in the low autonomy group will receive a pre-determined game.

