**D. Statistical Analysis Plan**

*Power analysis and sample size:*

Prior research has shown an effect size of approximately eta squared (h^2^) = 0.45 and a mean difference between high (M = 41.4) vs low autonomy (M = 22.5 minutes of play) conditions (difference = 18.9 minutes) (Roemmich et al., 2012). Based upon these and conservative estimates from Cohen’s guidelines for multivariate effects (Cohen, 1992), estimates of required sample size to achieve power exceeding the 1 - β = .90 level were run and a sample size of N = 25 participants per autonomy condition was recommended.

Independent variables will be the study condition of high vs. low autonomy (categorical variable) and time (categorical). Dependent variables will consist of total scores in RRV_video games,_ total scores in RRV_active games_, total weekly minutes of physical activity, total weekly minutes of AVG play, total weekly minutes of sedentary video game play, total weekly minutes of other screen-based sedentary activity, total weekly minutes of non-screen based sedentary activities, maximum level completed towards AVGs, maximum level completed towards sedentary video games, BMI/ weight loss, total energy expenditure, exercise self-efficacy, intrinsic motivation towards AVGs, intrinsic motivation towards exercise, intrinsic motivation towards sedentary video games, sweetened beverage/snack consumption (continuous variables). Participant exercise self-efficacy, parental exercise self-efficacy, and parental support for physical activity will be treated as moderating covariates (continuous).

*Preliminary Analyses:*

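### The protocol promises random assignment but names Taves minimization with no stated random element, so about 78% of assignments would be fully determined once a child's three factors are known

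*Protocol*

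**What the plan says.** Protocol section C.ii (Design) states: "Participants will be randomly assigned to a high autonomy group or a low-autonomy group". The same paragraph continues: "Participants will be blocked according to Taves minimization on gender (male vs female"). The other two factors are "BMI (above 85^th^ percentile vs. below 85^th^ percentile") and "baseline liking of AVG (7 and lower vs. 8-10 on 10 point Likert scale"). Section C.iv (Intervention) repeats that assignment is random. Neither section gives an assignment probability below 1, says who runs the minimization, or describes concealment.

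The factors become known in stages. Sex is known from the outset. Height and weight are measured at the first in-person visit, after consent (C.iii). Liking is rated later, under the baseline assessments of relative reinforcing value (RRV): "Participants will be asked to sample and rate their liking of four active video games (Appendix 12"). The two baseline RRV tests take place on separate days, and the intervention starts only after both.

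On staff knowledge of arm, C.iv says "A researcher will visit the home at baseline to explain the intervention, set-up the AVG system", and at each later exchange of games "children in the high autonomy group will be allowed to select their next game, while children in the low autonomy group will receive a pre-determined" one. The planned size is in section D: "a sample size of N = 25 participants per autonomy condition was recommended".

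**The concern.** Under Taves minimization each new child goes to the arm with the smaller sum of marginal totals at that child's factor levels. A coin is tossed only when the sums are equal. Taken literally, the named method leaves most children's assignments without any chance element, which does not fit the promise of random assignment in the same paragraph.

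The practical issue is predictability. Someone who knows the earlier children's arms and factor levels can work out the next arm whenever there is no tie. That opens a route, intended or not, to influence whether a family at the margin goes on, how a child is classed on liking, or how the remaining baseline steps are handled. The liking factor adds some latitude: children rate four AVGs, and the Design section does not say which rating sets the class. The primary hypothesis (H1a) rests on a voluntary-effort task, so differences between arms in motivation at entry would matter.

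**Working it through.** The protocol gives no figure for predictability, so there is none to reproduce. The check is a simulation of the method as named.

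**Inputs from the protocol**
- Three factors with two levels each (C.ii).
- 25 per arm, so N = 2 × 25 = 50 (D).
- No random element stated (C.ii, C.iv).

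**Assumptions not in the protocol**
- Factor prevalences: one sex 0.4–0.5, BMI above the 85th percentile 0.10–0.50, one liking level 0.10–0.80.
- Equal weights; factors independent, also tried with positive correlation.

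**Rule.** For a new child with levels x1, x2, x3, compute D = Σ over the three factors of (number in arm A at level xf − number in arm B at level xf). If D < 0 assign A; if D > 0 assign B; if D = 0 toss a fair coin. An assignment is fully determined when D ≠ 0.

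**Share determined, N = 50 (1,000–2,000 simulated trials per scenario)**

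| What is known of the new child, with a full tally of earlier children | Fully determined |
| --- | --- |
| Sex only | about 31–32% |
| Sex and BMI class | about 55% |
| Sex, BMI class and liking | 78–79% |

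The last row is a mean of 39 of 50 children (5th to 95th percentile 35 to 43). It stays at 78–79% across the prevalences tried, with correlated factors, and for N = 40 to 60. The Pocock–Simon absolute-difference measure gives 76–77%. Breaking ties on overall arm totals gives 85–87%.

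**Correct guesses with all three factors known.** Determined assignments are always guessed correctly and ties half the time: 0.784 + 0.5 × (1 − 0.784) = 0.892, or about 89%.

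**Effect of a random element.** If the minimizing arm is given with probability 0.8, ties become rarer (D ≠ 0 for about 84.2% of children), but no assignment is certain. Correct guesses: 0.842 × 0.8 + 0.158 × 0.5 = 0.674 + 0.079 = 0.753, or about 75%.

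| Probability of the minimizing arm | Correct guesses | Mean difference in arm size (children) |
| --- | --- | --- |
| 1 (as named) | 89% | 0.3 |
| 0.9 | 82% | 0.6 |
| 0.8 | 75% | 0.9–1.0 |
| 0.7 | 67% | 1.6 |

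Mean imbalance per factor level rises from about 0.6 to about 1.1 children when the probability goes from 1 to 0.8.

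**The case against.** **A random component may be intended.** The protocol says twice that assignment is random and never sets out the algorithm. This stands in part: a reader might infer that allocation will certainly be deterministic, and the text does not prove that. But the only method named is one that uses chance only at ties, and nothing qualifies it. If a random element is intended, stating it settles the point.

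**Who can predict is not documented.** A reader might infer that an unblinded study team will know about four in five assignments in advance. The protocol does not support that. It refers to a researcher, not to one team that screens, tests and visits homes, and it does not say who keeps the tally. A separate allocator holding the list would reduce the exposure considerably. What remains is that staff who carry out arm-specific procedures necessarily know those children's arms.

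**The 78% comes late.** It applies only once liking is rated, when the child has already consented. The order of bookings and initial recruitment are therefore less exposed than the headline share suggests.

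**The routes to bias are limited.** The child works alone at the RRV task with the researcher in an adjacent room, the liking score is the child's own, and the intervention waits for both tests. Planned adjustment for baseline variables handles measured differences. All of this is fair, though adjustment cannot correct selection on unmeasured traits, and the researcher still explains and demonstrates the task beforehand.

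**A probability of 0.8 still allows 75% correct guesses.** True. Concealment and late release are at least as important as the coin, which is why the fix includes both.

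**Conclusion.** The point holds as a mismatch between the promise and the named method, with a measurable exposure. Followed literally, the plan would leave about 78% of assignments (range 76–87% over the variants of the method) with no chance element once all three factors are known. A person with the full tally would guess about 89% correctly. These figures rest on equal weights, on chance acting only at ties, and on the guesser having a complete tally. The assumed prevalences barely move them.

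A reader might go further and infer that the comparison is biased. Nothing in the protocol shows that: predictability is an opportunity, and no effect on the RRV outcome or on the type I error has been derived. The exposure lies mainly in late baseline steps and in whether a child proceeds. This is an inexpensive improvement to make before enrolment, not a fatal flaw.

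**What to change.** In C.ii, keep the three factors and state a random element: for example, assign the minimizing arm with probability 0.8 and use 1:1 at ties. State which liking rating sets the 7/8 class. Name a person without family contact to run the allocation and hold the tally. Release each assignment only after both baseline RRV tests and the liking ratings have been recorded. Since C.iv already starts the intervention after both tests, the schedule does not change.

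The cost is a few protocol sentences and a small change to the allocation procedure. Balance loosens slightly: the mean difference in arm size goes from about 0.3 to about 1 child in 50, and mean imbalance per factor level from about 0.6 to about 1.1 children.

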**iii. Procedures:**

*Screening and Consent Visit:* Initial screening will take place online. The first in-person session will include a review of answers to the online screening questions (Appendix 1), study procedures, informed consent/assent and baseline measurements. After providing consent/assent, parents will be asked to fill-out a basic demographics questionnaire (Appendix 2) and health history questionnaire (Appendix 3) regarding their child. Youth will be measured for height and weight and the parents and children will work together to complete the first of 4 Survey Monkey-based 24 hour recalls (Appendix 4) assessing baseline time that the child spent in physical activity, sedentary video games, and other screen-based sedentary activities. Baseline physical activity and sedentary behavior will be further assessed by having the participants wear an activity monitor (ActiGraph WGT3X-BT) for seven days and fill out a 24 hour activity recall on three more days, including a weekend day. Using questionnaires, children will be measured for their exercise self-efficacy (Appendix 5), intrinsic and extrinsic motivation for exercise (Appendix 6), intrinsic and extrinsic motivation for AVG (Appendix 7), intrinsic and extrinsic motivation for sedentary video games (Appendix 8), and snack/ sweetened beverage consumption (Appendix 9). Parents will also be asked to complete a series of questionnaires measuring their support of their child’s physical activities (Appendix10), and self-efficacy for their own exercise habits (Appendix 11). Parents will be permitted to assist their child completing the surveys if necessary.

*Baseline RRV Assessments:* RRV assessments will take place in the Grand Forks Human Nutrition Research Center (GFHNRC) laboratory space at Choice Health and Fitness Center. On separate days children will be assessed for their relative reinforcing value of active to sedentary video games (RRV_video games_) and RRV of active video games to traditional active games (RRV_active games_). Order of these tests will be counterbalanced among participants. Participants will be asked to sample and rate their liking of four active video games (Appendix 12), four inactive video games (Appendix 13), and four traditional games/sports (Appendix 14). Children will be permitted to briefly sample games with which they are not familiar. Following the RRV task, children will be permitted to play the games corresponding to time earned on the task. Active and sedentary video games shall be played at Choice Health and Fitness spaces. Participants and their parent will complete a 24 hour recall assessing baseline time spent in physical activity, sedentary video games, and other screen-based sedentary activities at the end of one of these visits. Parents and children will complete the 3^rd^ and 4^th^ of the 4 recalls during weekend days at home using SurveyMonkey.

*Week 1 and 3 Assessments:* Children will wear an activity monitor for 7 consecutive days in the same manner as at baseline assessment. Participating parents and children will also be asked to fill-out the 24 hour activity recall on 4 days, including at least one weekend day.

*End of-intervention (Week 6) Assessments:* Outcome assessments will take place during and just after the last week of the 6 week intervention. Post-intervention anthropometry, questionnaire, RRV, and physical activity testing will be identical to screening/baseline assessments.

*4 Week (Week 10) Post-Intervention Follow-up Assessments and Debriefing:* At 4 weeks following the end of the intervention, participants will complete their final assessment, to determine whether intervention effects on videogame reinforcement, AVG use, physical activity reinforcement, physical activity, and sedentary behavior have been maintained for at least 4 weeks. The assessments will be identical to screening/baseline. Following the assessment, participants will be debriefed, asked for intervention feedback (Appendix 15 & 16), thanked for their time, and compensated.

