**Usual Physical activity.** PA will be assessed with the ActiGraph WGT3X-BT monitor. The device has a 3-axis accelerometer to collect measures of raw acceleration, and PA amount and intensity, and sedentary time. The ActiGraph has been extensively used in research studies and validated for use in children ages 8-12 (Ekelund et al., 2001; Puyau, 2002; Trost et al., 1998) Children will be instructed to put the ActiGraph on upon waking and only take it off while sleeping or in water-based activities. Parents will be trained regarding the importance that their child wears the ActiGraph at least 10 hours/day (standard to ensure validity) including the times that they play AVG for 7 consecutive days during the indicated study periods. Parents will receive written instructions on use, including appropriate care and placement on the right iliac crest (a belt is provided) (Appendix 18) (Patterson et al., 1993). The ActiGraph will be initialized for 5 second epochs and the data downloaded using the ActiLife software and stored in a “dat” file. Then, a customized Systat code will be used to identify spurious data of >16,000-20,000 counts, negative counts, and strings of identical counts. It will score sequences of 20 + minutes of consecutive zero counts as non-wear time. The total amount of PA from the activity monitor will be expressed as the average of total counts per minute of time worn. The main outcome variables will be mean counts/minute an index of mean total PA and time spent in moderate to vigorous PA (MVPA). The ActiGraph data will be converted to 15-sec epochs and MVPA determined using the count thresholds developed by Evenson et al. (2008; Trost et al., 2011).

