**Physical Activity Mode and Sedentary Activity.** Physical activity and sedentary activities will be primarily assessed using the accelerometers. However, accelerometers do not provide detail of the mode of physical activity or sedentary behavior. As an adjunct, children will complete a 24 hour recall based upon the procedures described in Simons and colleagues (2015). Children will be asked to indicate for three time periods (awakening to noon, noon to 4 PM, and 4 PM until bedtime) how much time they had spent in a predetermined list of activities including active video games, sedentary video games, other screen-based sedentary activities (TV, computer, IPad), non-screen based sedentary activities (homework, music/art lessons), physical activity (sports, physical education classes), and other physical activity (chores, walking to school) (see Appendix 4). Categories will be slightly modified from the original study to make them age-appropriate. Participants will complete the recall on 4 days, including two school-days and two weekend days. The participating parent will be sent text and/or email links to the recall on Survey Monkey, so that they may fill out the recall at the end of each day. Parents will be encouraged to work with their child to complete the recall.

**Beverage and Snack Consumption.** To measure non-meal snacking during playtime or games, children will be administered the Beverage and Snack Questionnaire (BSQ) (Neuhouser et al., 2009). This tool consists of 19 questions designed to measure consumption of common sugar-sweetened beverages and snack foods, both in school and at home. The tool was designed for school-aged children (mean age = 12.7). Validation studies have found this measure to have good reliability and validity (Neuhouser et al., 2009) (see Appendix 9).

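### One 24 hour recall is completed at the end of an RRV visit where earned AVG time has just been played, so H1d can be partly confirmed by the measurement visit itself

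*Protocol*

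**What the plan says.** Section C.iii (Baseline RRV Assessments) has earned time played at the visit: "Following the RRV task, children will be permitted to play the games corresponding to time earned on the task". The same paragraph attaches one of the four recalls to such a visit; the sentence that does so closes with the words "and other screen-based sedentary activities at the end of one of these visits". The third and fourth are "recalls during weekend days at home using SurveyMonkey".

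For week 6, "Outcome assessments will take place during and just after the last week of the 6 week intervention", with procedures identical to baseline. Week 10 is also identical to baseline.

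Section C.v (Physical Activity Mode and Sedentary Activity) lays the recall out in "three time periods (awakening to noon, noon to 4 PM, and 4 PM until bedtime", to be filled in at the end of each day on two school days and two weekend days. Active video games are a listed category.

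Section C.v (AVG Reinforcement Task) gives play in five-minute units for each five points, on schedules doubling from 4 to 1024 presses per point. Section C.iv introduces the home play log as a check of fidelity. Section D lists total weekly minutes of AVG play as a dependent variable without naming its source.

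**The concern.** H1d is meant to show that autonomy carries over to more AVG play in the follow-up phase. Play at the centre is a different quantity: it is the payout of the reinforcement task, fixed by how many schedules the child completed. If the recall counts those minutes, an arm that works harder for AVGs in the task automatically reports more AVG play, even if nothing has changed at home.

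Randomisation does not remove this, because the minutes arise after randomisation from the outcome under test. H1d would be contaminated exactly when H1a is true, and would stop being separate evidence about behaviour outside the laboratory.

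**Working it through.** **1. Does the recall include the visit?** The protocol allows three readings.
- Rolling 24 hours back from completion: includes the visit.
- Same calendar day, as in the general rule of C.v: includes the visit, although a form completed at the end of a visit cannot yet cover the time until bedtime.
- Previous day only: avoids the problem, but is not stated.

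**2. Which day is it?** Recalls 3 and 4 are weekend days at home, and C.v asks for two school days and two weekend days. The visit recall is therefore most naturally one of only two school-day recalls.

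**3. Minutes at the centre.** The levels 4, 8, ..., 1024 number 9, at 5 minutes each. A gap of two completed levels between arms (assumed; the protocol gives no expected gap) is 2 × 5 = 10 minutes.

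**4. Scaling to a week.** The protocol gives no weighting, so three are shown.
- Visit on a weekend day, weekly total = 5 × school-day mean + 2 × weekend-day mean: 10/2 × 2 = 10 min/week.
- Simple four-day mean × 7: 10/4 × 7 = 17.5 min/week.
- Visit on a school day, 5/2 weighting: 10/2 × 5 = 25 min/week.

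The yardstick is the minimum instructed in C.iv for the intervention: 3 × 20 = 60 min/week. No amount is prescribed in the follow-up phase.

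**5. Effect on the H1d test.** The calculation uses a two-sided t test at 0.05 (sidedness assumed) with 25 per group and no true difference at home. The protocol gives no SD for weekly AVG minutes, so SDs are assumed.

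| Spurious difference | SD 30 | SD 60 | SD 90 |
| --- | --- | --- | --- |
| 10 min/week | 21% | 9% | 7% |
| 17.5 min/week | 52% | 17% | 10% |
| 25 min/week | 82% | 30% | 16% |

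If the arms do not differ on RRV, or centre play is excluded, the rejection rate is 5%.

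**6. H1e (monitor).** Suppose the monitored week overlaps a visit and the arms differ by 20 minutes at the centre. Then 20/7 = 2.9 min/day, or 20/4200 = 0.5% of 70 hours' wear. Rejection is 17% at an assumed SD of 10 min/day and 8% at 20, even if every minute counts as MVPA.

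**7. H2b.** The predictor in section D is change in AVG Pmax, and AVG minutes do not enter sedentary game minutes. Only sedentary play at the centre does. Take an assumed SD of 10 minutes for it, × 2.5 = 25, an assumed home SD of 100 to 400 min/week, and a correlation r between AVG and sedentary Pmax. The induced correlation is r × 25/√(25² + SD²). At r = +0.5 it is +0.12 to +0.03, at r = 0 it is nil, and at r = −0.5 it is −0.12 to −0.03.

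**The case against.** The strongest reply is that overlap is not documented. A form running from waking to bedtime cannot be finished at a visit, so the previous day may be intended, and the recall form (Appendix 4) is not among the pages at hand. The log also continues through the post-intervention period and could supply the H1d minutes. These points stand as conditions on the conclusion. They do not remove it: two of the three readings include the visit, and the log's only stated purpose is fidelity. It is also true that at most one recall in four is affected, and that bias in H1d needs a real RRV difference.

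A reader might infer more than the text supports:
- **That visits fall inside the monitor period.** C.v asks for wear "including the times that they play AVG for 7 consecutive days during the indicated study periods", but this concerns wear in general. The timing of week 6 also permits monitoring during the week and RRV testing after it. Overlap is possible, not stated.
- **That H1e would be falsely confirmed.** The effect is small. In the task against traditional games, more AVG time may displace play that section A says expends more energy, so even the sign is uncertain.
- **That H2b gains false support.** The induced correlation has no fixed direction and can oppose the hypothesis.
- **That centre play could reach 9 × 5 = 45 minutes, or 45 × 7/4 = 79 min/week.** Nine levels need 5 × (4 + 8 + ... + 1024) = 10,220 presses. Table 2 allots 60 minutes per session, which would mean 10,220/3600 = 2.8 presses per second throughout. That is hardly feasible.

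The two-level gap is itself a fourfold difference in presses per point, so it is an illustration and not a forecast.

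**Conclusion.** The point holds for H1d, conditionally. As scheduled, a recall can count AVG minutes set by the RRV result. With an assumed two-level gap this adds about 10 to 25 min/week to the difference between arms, the upper figure applying if the visit recall is a school day and days are weighted 5/2. The chance of a false H1d result then ranges from slightly above 5% to 82%, depending mostly on an SD that the protocol does not give.

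This rests on three conditions: the recall window includes the visit, weekly AVG minutes come from the recall, and the arms differ in AVG responding at the task to which the recall is attached. The protocol does not say which of the two RRV visits that is; at the visit with traditional games the coupling would be to the H1f outcome.

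The primary H1a analysis is unaffected. The matter deserves correction in the protocol because it concerns data collection: minutes not separated when the recall is completed may not be separable later.

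**What to change.** In section C.iii, for baseline, week 6 and week 10:
- Move the recall now completed at an RRV visit to a school day without an RRV visit. Alternatively, instruct families to leave out play at the centre.
- State the window that each recall covers.
- State that weekly AVG minutes mean play outside the centre, and name the source.
- Where monitor days overlap an RRV visit, record the visit's start and end times and drop that window from the monitor data.

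The cost is slight scheduling effort, a line in the recall instructions, and an hour or two of monitor data lost on visit days.
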